### Methods: assignment of interventions

#### Allocation

For allocation to treatment and control group, a randomly permuted block randomization with varying block size stratified by site is used to assign patients in a 1:1 ratio by an online randomization service (www.randomizer.at). Care providers are instructed to log in to an online interface to receive allocation after completing baseline assessment. After completion of the first telephone interview with the local research associates, patients are informed about allocation by HT care providers at their subsequent visit.

#### Blinding

HT care providers and patients are blinded at time of baseline ratings (GAF; CGI). Randomization and allocation to treatment are done after baseline rating. For compelling reasons, HT care providers’ second rating of GAF and CGI at time of discharge is not blinded nor are patients at further times of data acquisition because they will have received intervention. Research associates accomplishing telephone interviews are blinded whenever possible. That is, at all four measurement points, namely at admission (t_0_), 2 months after admission (t_1_), 6 months after admission (t_2_), and 12 months after admission (t_3_). In telephone interviews at t_1_, t_2_, and t_3_ patients are explicitly instructed not to reveal any information about their group allocation against research associates to ensure blinding of outcome assessment. The statistical analysis will be conducted in a blinded manner.

### Methods: data collection, management, analysis

#### Data collection methods

Data are collected at baseline by HT staff and research associates, at time of discharge by HT staff, and at the three follow-ups (at 2, 6 and 12 months) by local research teams.

#### Primary outcome

Data on *time to first readmission to inpatient hospital treatment* is collected from the respective hospital IT database. According to the intention-to-treat analysis, primary outcomes of all participants are collected – also in case of dropout from treatment or follow-up assessment.

#### Secondary outcomes

The main part of data collection of secondary outcomes is carried out by research associates using four telephone interviews lasting between 30 to 45 min. They take place at time of enrolment and at a 2-months, 6-months, and 12-months follow-up. To provide a standardized procedure for research associates, a guideline for instruction of telephone interviews was prepared and trained. To facilitate oral self-ratings for participants, visual response scales are handed out in advance.

At time of enrolment, *socio-demographical data* (age, gender, domestic and occupational circumstances) and *information about previous HT and PS* and *current diagnoses* of participants are collected by local HT care providers, as well as ratings of CGI and GAF. HT Care providers are trained in GAF ratings if not used to it or GAF ratings had not been implemented to clinical routine before. At the end of the treatment, care providers again rate CGI and GAF. Additionally, it is registered *how treatment was concluded* (regular discharge/ termination of treatment by clinicians/ drop-out by patient/ in-house admission) and if there was a *change in diagnosis*. Furthermore, *days of treatment, number of treatment contacts, and duration of treatment contacts* are recorded for each participant. For patients having received PS, *treatment day of first PS contact, number of PS contacts* (1:1, within the HT team, in a group setting*), number of aftercare PS contacts* and *duration of PS contacts* are additionally recorded.

#### Safety outcomes

Safety outcomes (i.e. adverse events, AEs) will be recorded as part of the regular documentation. As such, we do not expect major adverse events, especially none caused by the intervention (peer support). However, in terms of assessment of safety and harms, we will record and report dropout from study, diagnosis pre/post, type of discharge from treatment (as planned/early termination by patient or team/admission to inpatient treatment), severity of mental disorder (CGI and GAF, pre/post), hospital admissions due to somatic diseases, and death.

#### Data management

After having given written informed consent, each participant receives a subject ID stored in a locked key list. All data acquired will be stored and locked solely with this ID that does not contain any patient identifying information. Data will be stored according to a data management plan ensuring data security.

Data entry will be prepared by the coordinating study site at the UKE Hamburg by establishing a common template for data input from telephone interviews. Where possible, the research associates at each study site will enter their acquired data directly, otherwise this will be done centrally. The paper version of the interviews will be stored until all final check-ups have been conducted.

### Statistical methods

Patients will be described with respect to relevant baseline characteristics, both overall and separately for the two randomized groups. Categorical data will be summarized by numbers and percentages. Continuous data will be summarized by mean, standard deviation, median, inter-quartile-range, and range. The number of available observations and the number of missing observations will be presented separately for the treatment groups. Tests of statistical significance will not be undertaken for baseline characteristics; rather the clinical importance of any imbalance will be noted [54].

The intention-to-treat analyses of primary data will be based on the available clinical data from all randomized patients. Only the primary analysis will be treated in a confirmatory manner. The aim is to show a difference between the peer-supported HT group compared to the professional-led HT group with respect to the primary endpoint. For the primary endpoint, a stratified logrank test for a comparison of the treatment groups with strata defined by study center will be performed. The two-sided type I error will be set at 5%. A stratified (stratum = study center) Cox proportional hazard model will be applied to estimate a treatment effect (hazard ratio). The hazard ratio will be reported along with the corresponding 95% confidence interval. An additional analysis will be conducted on a per-protocol (PP) analysis set. The PP population consists of the complete cases without severe protocol violations. Severe protocol violations are defined according to the intervention protocol, e.g. too few peer contacts in the intervention group (HT plus PS). Extended analyses (ITT-population) with inclusion of several covariates will be performed using the stratified Cox model. In particular, patient sex will be included as a covariate, and an interaction term sex*intervention will be added to the model for subgroup analysis. Besides patient sex, further covariates/subgroups include patient age, main diagnosis, composition of household (living alone/with partner/with kids etc.), occupational situation, severity of mental disorder (according to CGI and GAF) at admission, earlier exposure to peer support (j/n), and location of psychiatric clinical center (North/South/East and rural/urban).

The secondary endpoints will be examined in an exploratory manner with linear mixed models. In case of skewed distributions, transformations will be considered (e.g. log-transformation). In case of zero-inflated data, mixed zero-inflated models or negative binomial models will be used.

Safety outcomes (i.e. adverse events, AEs) will be determined by group using frequency tables and if possible using logistic regressions to compare the event frequencies. Interim analyses are not planned. A data safety monitoring board will not be involved. A detailed statistical analyses plan will be prepared and finalized before the code is broken. Data will be analyzed according to the CONSORT (*Consolidated Standards of Reporting Trials)* statement [55]. Statistical analyses will be carried out with an established statistical software such as R (R Foundation for Statistical Computing) or SAS (Cary, NC: SAS Institute Inc.). The final dataset is only accessible for the researchers conducting the analysis at the Department of Medical Biometry and Epidemiology at University Medical Center Hamburg-Eppendorf.

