### Recruitment

Patients regularly admitted to HT at one of the eight participating study sites and fulfilling eligibility criteria are informed about the study by care providers at time of admission. In most cases, patients are directly admitted. Nonetheless, it is also possible that they are transferred from inpatient treatment to HT. Patients receive verbal and written information about the study. If study information is not possible due to acute symptom severity, admission to the study can be delayed for up to 14 days until informed consent can be given. Until enrolment to the study, these patients receive standard HT care without involvement of peers. For enrolment, a minimal planned duration of treatment of two (further) weeks or ten home visits is predefined. Before giving written informed consent, patients have the possibility to additionally consult local research teams for patient information. This offer holds for the duration of the entire study. After having given written informed consent, care givers contact the local research team, who is then conducting the first telephone interview (see below). Study participation is voluntary. If negated or in case of dropout, patients receive treatment as usual by the HT team without any harm. The recruitment period continues for up to 18 months at each site to reach an average target sample of 36 participants per site.

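### The sole confirmatory test adjusts for centre only; adding a few covariates recorded before allocation would be a cheap gain in efficiency, not the repair of an error

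*Protocol article*

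**What the plan says.** All of the following is in the protocol article.

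- **Confirmatory test** (Statistical methods): "Only the primary analysis will be treated in a confirmatory manner". For the primary endpoint, time to first inpatient readmission, "a stratified logrank test for a comparison of the treatment groups with strata defined by study center will be performed", two-sided at 5%.
- **Effect estimate** (same section): "A stratified (stratum = study center) Cox proportional hazard model will be applied to estimate a treatment effect (hazard ratio"). No patient-level covariate is named for this model.
- **Adjusted analyses** (same section): "Extended analyses (ITT-population) with inclusion of several covariates will be performed using the stratified Cox model". The variables named there include sex, age, main diagnosis, and CGI and GAF at admission.
- **Availability of the covariates**: the Secondary outcomes section on data collection says that sociodemographic data and current diagnoses "of participants are collected by local HT care providers, as well as ratings of CGI and GAF", at enrolment. The Blinding section places the baseline CGI and GAF ratings before randomisation. The Allocation section says that the assignment is obtained only once the baseline assessment is complete, and that randomisation is stratified by site alone.
- **Sizing** (Sample size): 254 patients and 106 events for 80% power with the logrank test. The chosen total of 286 comes from the secondary continuous outcomes.

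**The concern.** Eligibility spans ICD-10 groups F2, F3, F6, F41 and F42, so the risk of readmission may well differ considerably between patients of the same centre. Neither the randomisation nor the confirmatory test uses any patient-level predictor of that risk. If the recorded variables do predict readmission, a test that ignores them has less power than one that uses them. The adjusted Cox model already planned cannot make up for this, because it lies outside the confirmatory claim. At stake are some points of power for the trial's one confirmatory question, and some precision in its estimate.

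**Working it through.** **1. The plan's own figures.** Inputs from Sample size: 58% and 73% free of admission at one year, 30% loss over two years, 12 months of accrual, minimum follow-up of 12 months.

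- HR = ln(0.73)/ln(0.58) = 0.578 (stated: 0.577).
- Events (Schoenfeld, two-sided 5%, 80% power) = 4(1.960 + 0.842)²/(ln 0.577)² = 104 after rounding up (stated: 106).
- Yearly hazards: control -ln(0.58) = 0.545; intervention -ln(0.73) = 0.315; loss -ln(0.7)/2 = 0.178. With uniform accrual the event probabilities are 0.493 and 0.331.
- Expected events at N = 254: 127 × (0.493 + 0.331) = 104.6. To reach 106 events takes N = 257, within about 1% of the stated 254.

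The calculation reproduces.

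**2. Power at the chosen N.** Expected events at N = 286: 143 × (0.493 + 0.331) = 117.8. Schoenfeld power = Φ(√117.8 × 0.550/2 - 1.96) = Φ(1.02) = 84.7%. Simulated power of the site-stratified logrank test is a little lower, about 81% to 83%. Both exceed 80%.

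**3. What adjustment would change.** The documents give no prognostic strength, so the SD of the covariate log-hazard score is an assumption, varied from 0 to 1.0 (hazard ratio per SD from 1.0 to 2.7). Both simulations use eight sites, allocation stratified by site, exponential hazards calibrated to marginal one-year rates of 58% and 73%, and 3000 runs per cell (standard error about 0.7 points). N = 286:

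| Simulation | Assumed SD | Plain stratified logrank | Adjusted | Change (points) |
|---|---|---|---|---|
| A: five covariates, two informative | 0 | 83.1% | 81.9% | -1.2 |
| A | 0.4 | 82.3% | 84.5% | +2.2 |
| A | 0.6 | 81.0% | 84.6% | +3.6 |
| A | 0.8 | 80.7% | 87.4% | +6.7 |
| B: six covariates, adjusted stratified Cox Wald test | 0 | 82.6% | 82.0% | -0.6 |
| B | 0.3 | 83.1% | 83.9% | +0.8 |
| B | 0.5 | 81.7% | 85.0% | +3.3 |
| B | 0.7 | 80.6% | 87.9% | +7.3 |
| B | 1.0 | 81.2% | 92.6% | +11.4 |

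A separate simulation of the covariate-adjusted logrank test gave gains of about 3 to 7 points for SDs of 0.4 to 0.8. The top figure of +11 comes from the Cox Wald test at the strongest assumption.

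**4. Type I error.** In simulation B it was 5.1% to 5.3% for the plain test and 5.0% to 5.7% for the adjusted Cox test. In simulation A the adjusted test gave 4.6% to 4.9%. With eight model terms (CGI, GAF, age, sex, and four indicators for five diagnosis groups) the adjusted logrank test gave 5.2% to 5.4%, against 4.3% to 4.7% for the plain test (10,000 runs per cell).

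**5. Chance imbalance.** The SD of a standardised baseline difference is 2/√286 = 0.118. With a prognostic SD of 0.6, the 95% range of the shift in log HR is ±1.96 × 0.6 × 0.118 = ±0.14. The standard error of the log HR is about 2/√118 = 0.184, a 95% range of ±0.36. The share of variance is (0.6 × 0.118)²/0.184² = 0.0050/0.0339, about 15%. This is part of the sampling variance already counted in the power figures, not an addition to it.

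**6. Estimand.** In simulation B at SD 0.5 the mean hazard ratio was 0.58 unadjusted and 0.55 adjusted. The adjusted Cox hazard ratio is a conditional effect and lies further from 1.

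**The case against.** The plan states nothing wrongly. Its strata match the randomisation strata, its test is the one used for sizing, and a valid standard test is not badly chosen merely because a more efficient one exists. The gain rests entirely on an assumed prognostic strength, and with uninformative covariates it turns into a small loss. An adjusted model in the ITT population is already planned, so readers will see an adjusted hazard ratio. All of this stands, and it makes the point a recommendation. It does not remove the point: the confirmatory label decides the trial's claim, the data are collected anyway, and the possible loss is small beside the possible gain.

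Three stronger readings are tempting, and the documents support none of them:

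- *The trial is underpowered or loses power for certain.* The plain test reaches 80% at N = 286 for every SD assumed. Simulated power falls to 75% to 79% only at N = 254, which is not the chosen size. No document gives the prognostic strength that would turn a possible loss into a known one.
- *Chance imbalance biases the test.* Type I error of the plain test stays nominal. Imbalance moves the single-trial estimate within its ordinary sampling error.
- *The covariate list is deficient because it lacks route into HT and earlier inpatient stays.* Recruitment does say "it is also possible that they are transferred from inpatient treatment to HT", and readmission data "is collected from the respective hospital IT database". But the list is worded as inclusive rather than exhaustive, its detail may belong to the SAP, and nothing says that the hospital system holds earlier stays for every patient.

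**Conclusion.** The point holds as a low-cost improvement in efficiency. The confirmatory analysis is valid, reproduces on its own assumptions and meets its stated power at N = 286. Making a prespecified covariate-adjusted test confirmatory would change power at that size by about -1 to +11 points over assumed SDs of 0 to 1.0, and by about +2 to +7 for SDs of 0.4 to 0.8. These figures rest on the planning rates, a 12-month accrual, exponential hazards and, above all, a prognostic strength that the documents do not supply. The benefit for type I error is nil.

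**What to change.** Before unblinding, in the analysis plan that the protocol says is still to be finalised:

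1. Make the confirmatory test a covariate-adjusted logrank test stratified by centre, two-sided at 5%. It tests the same null hypothesis as the planned test.
2. Fix a short covariate list: baseline CGI, baseline GAF, broad main diagnosis group as recorded at enrolment, age and sex. Keep the number of model terms small, by merging diagnosis groups, so that type I error stays near 5%.
3. Keep the plain centre-stratified logrank test as a sensitivity analysis.
4. Report the centre-stratified unadjusted hazard ratio together with the covariate-adjusted one, and label the latter as a conditional effect.
5. State a simple rule for missing covariate values.

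The change needs wording only and no new data. Its price is about 1 point of power if no covariate is prognostic, and possibly a slight rise in type I error if many terms are used.

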### Interventions

Patients in the *intervention group* receive a combination of HT by a multi-professional team with PS: PS workers are involved during the whole treatment duration. After discharge a maximum of five additional contacts are possible. Contacts to a PS worker take place at least one time per week in 1:1 contacts or in combination with other members of the HT team. Important aspects of PS contacts are defined as focus on personal resources, support of self-determination and autonomy, practical support in daily tasks, recover- and need-orientation, building bridges between patients and care providers, and trialogical work with inclusion of relatives or close persons. The so-called ‘trialogue’ format [42] is a term used in Germany to designate discussion meetings involving peers, carers and professionals focusing on the experience of, coping with, and recovery from mental health problems with special attention to the peer, carer and professional perspectives, contrasts, differences and perhaps similarities in experience. As far as possible (e.g. due to limited working hours), PS workers are included into all relevant treatment decisions. To ensure a standardization of treatment, an intervention guideline was established together with PS workers. Furthermore, there was an online training for PS workers regarding relevant aspects of peer work and the peer role within the intervention. All eligible PS workers had to have completed a standardized PS training, e.g. *Ex-In (Experienced Involvement)* [24] or *Honest, Open, Proud* [31, 43].

The *control group* receives conventional HT by a multi-professional team without contacts to a PS worker (treatment as usual). Multi-professional teams consist of nursing staff, psychiatrists/physicians, occupational therapists, social workers, and psychologists/psychotherapists. They provide acute mental health treatment by mobile care teams within the patients’ home setting or familiar environment that is equivalent to inpatient treatment (i.e. crisis intervention, supportive and therapeutic conversations, pharmacotherapy, support in daily life and problem solving, transfer to outpatient care and support [1, 44].

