### Sample size

For the purpose of sample size calculation, data for the HT alone group were collected from routine data of University Medical Center of Hamburg-Eppendorf, Department of Psychiatry and Psychotherapy. For the HT plus PS group data was collected from a former in-house study (unpublished routine data). From these data, one-year admission-free survival rates of 58% and 73%, respectively, were calculated corresponding to a hazard ratio of 0.577. To detect a difference between random groups of this order of magnitude with a power of 80%, *N* = 254 patients in total (127 patients per group; total event count = 106) are required if the recruitment takes 12 months and there are at least 12 months follow-up to an administrative censoring. This calculation includes a 30% loss-to-follow up over two years of follow-up time. With an accrual period of 18 months and the same assumption as above a sample size of *N* = 232 (total event count 106) is needed. This latter analysis was only added since recruitment intensity might be low due to COVID-19 restrictions. Additionally, it was checked how many patients would be needed to demonstrate a medium effect size (Cohen’s d = 0.4) with a power of 80% and a two-sided type I error of 5% in the secondary continuous outcomes. This resulted in 100 patients per group (200 patients in total) and with an expected dropout rate of 30%, in 286 patients in total (143 patients per group). Therefore, the total sample size of 286 was chosen. Sample size was calculated with PASS 2008 based on the logrank test (using proportion surviving) [53] and the two-sample t-test using an effect size.

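### The one named per-protocol exclusion, too few peer contacts in the HT plus PS arm, can be caused by the primary event itself; applied as a minimum count it would tilt the PP hazard ratio towards peer support

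*Protocol article*

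**What the plan says.** In the Protocol article, Statistical methods, the confirmatory analysis is a stratified logrank test on all randomised patients, with a stratified Cox model for the hazard ratio. A PP analysis is added, and its set is defined in two sentences: "The PP population consists of the complete cases without severe protocol violations" and "Severe protocol violations are defined according to the intervention protocol, e.g. too few peer contacts in the intervention group (HT plus PS". No number of contacts is given.

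Other sections bear on how this works:
- **Interventions:** "Contacts to a PS worker take place at least one time per week", during a treatment lasting from two to several weeks. Up to five contacts are possible after discharge. Patients readmitted within six months of enrolment get their allocated intervention again. Controls are to have no peer support throughout.
- **Abstract (Methods) and Outcomes:** the endpoint is the first hospitalisation after randomisation, so an admission during the index HT episode counts.
- **Secondary outcomes (data collection):** in-house admission is one of the recorded ways in which HT ends. Treatment days, number of peer contacts and treatment day of the first peer contact are also recorded.
- **Primary outcome (data collection):** the endpoint comes from the hospital database for all participants, including those who drop out.

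**The concern.** Peer contacts build up week by week while HT lasts. A patient moved to a ward in week two has had the primary event and, for that reason, has few contacts. In the HT plus PS arm such a patient could be classed as a severe violator and removed. A control with the same early admission has no contact criterion to fail and stays. The exclusion then depends on the outcome and acts on one side only.

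Complete cases raises a separate question. A censored survival time is a usable observation, and the endpoint is collected on everyone. The condition therefore either excludes nobody or, if it refers to the telephone interviews, excludes patients whose primary outcome is known. The text does not say which.

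At stake is the only adherence-based analysis of the primary comparison that the article describes. A PP hazard ratio more favourable than the ITT one could be taken as a sign that peer support works when delivered properly, when the exclusion rule alone produced the difference.

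**Working it through.** **Reproducing the plan's own figures.** Sample size states "one-year admission-free survival rates of 58% and 73%, respectively, were calculated corresponding to a hazard ratio of 0.577". Check: ln(0.73)/ln(0.58) = 0.578. Schoenfeld events for 80% power at two-sided 5%: 4 × (1.960 + 0.842)² / (ln 0.578)² = 104.3, so 105. The article has "127 patients per group; total event count = 106) are required if the recruitment takes 12 months", and "This calculation includes a 30% loss-to-follow up over two years of follow-up time". A Lakatos-type calculation with that loss gives 106.1 events and N = 258 against the stated 254. The sample size is sound, so its inputs can be reused.

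**Inputs for the PP check, no true effect**
- Hazard in both arms: λ = −ln(0.58) = 0.545 per year (Sample size; constant hazard is an assumption).
- Loss: η = −ln(0.70)/2 = 0.178 per year (Sample size).
- Follow-up uniform on 1 to 2 years (12 months' accrual plus at least 12 months).
- Assumed rule: an HT plus PS patient admitted before week k is excluded for too few contacts; controls are not. The values k = 2 to 6 are not in the article.

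**Hand approximation.** Expected event proportion per arm: D = λ/(λ+η) × [1 − (e^−(λ+η) − e^−2(λ+η))/(λ+η)] = (0.545/0.723) × (1 − 0.345) = 0.493. Proportion admitted before week k: f = 1 − exp(−λk/52.18). The excluded patients are all events and add almost no follow-up time, so PP HR ≈ 1 − f/D.

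| k (weeks) | f | 1 − f/D | simulated PP HR |
|---|---|---|---|
| 2 | 0.021 | 0.958 | 0.965 |
| 3 | 0.031 | 0.938 | 0.938 |
| 4 | 0.041 | 0.917 | 0.921 |
| 6 | 0.061 | 0.877 | 0.881 |

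The last column is a Cox model on 400,000 simulated patients. The full-sample HR in those runs was 1.000 to 1.007.

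**Variations on the simulation**
- Same early-admission exclusion in both arms: PP HR within about 0.01 of the ITT HR. The asymmetry causes the shift.
- Assumed threefold hazard in the first six weeks: 0.90, 0.85, 0.81 and 0.72 for k = 2, 3, 4 and 6.
- True HR 0.577: PP HR 0.56 to 0.51 (constant hazard) or 0.52 to 0.43 (threefold early hazard).
- Chance of a PP result falsely favouring peer support at N = 286 (2,000 trials each; nominal 2.5%): 5% at k = 2 to 11% at k = 6 with constant hazard; 9% to 43% with threefold early hazard.
- Shortfalls unrelated to admission, 15% of the HT plus PS arm excluded: no shift.
- 15% of that arm excluded, all from the better-prognosis half (gamma frailty assumed): about 1.10, against peer support; combined with the k = 4 rule, about 1.01. All from the worse half: about 0.91 and 0.84.

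**Count rule against rate rule.** A separate simulation generated weekly contacts directly. Its assumptions were each contact kept with probability 85%, mean planned HT of 6 weeks, and 6.1%, 10% or 15% admitted within six weeks.

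| Rule | 6.1% | 10% | 15% |
|---|---|---|---|
| at least 3 contacts | 0.938 | 0.898 | 0.842 |
| at least 4 contacts | 0.916 | 0.864 | 0.797 |
| at least 60% of completed HT weeks | 0.995 | 0.998 | 0.994 |

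Only the 6.1% column matches a constant hazard at 58% one-year survival (f = 0.061 at six weeks).

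**The case against.** The strongest reply is that the article fixes no count. It refers violations to the intervention protocol, offers too few contacts as an example, and promises a detailed analysis plan before the code is broken. Neither document is shown, and the threshold may properly sit there. The only contact standard in the article is a weekly rate, which an early-admitted patient could have met, and a rate rule shows almost no shift. This stands: a missing threshold is no finding, and the bias is conditional on how the rule is applied.

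A reader might infer that the PP hazard ratio is certainly biased in favour of peer support, or that only HT plus PS patients can leave the PP set. The article supports neither. The example leaves room for control violations such as receiving peer support, and the complete-case condition covers both arms, although such exclusions would not mirror the loss of early-admitted patients. Complete cases does not itself remove those patients, since an observed admission is a complete outcome. Few contacts may also mean a short, successful treatment, which pushes the other way. Contacts after discharge or on readmission could let some early-admitted patients still reach a count.

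Nor is the PP analysis the only support for the primary result. Covariate-adjusted Cox models on the ITT population are also planned, and only the primary analysis is confirmatory.

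The constant-hazard shift is also modest beside sampling error. With 106 events the standard error of the log hazard ratio is about 2/√106 = 0.194, so 0.96 and 0.88 lie 0.2 and 0.7 standard errors from 1.

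What survives is that the form of the exclusion is already stated: it is named for one arm and can be triggered by the endpoint. An analysis plan that turned it into a simple count would follow this text and inherit the distortion.

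**Conclusion.** The concern holds in conditional form. If the contact criterion is applied as a minimum count in HT plus PS alone, a null PP hazard ratio moves to about 0.96 to 0.88. This assumes cut-offs of 2 to 6 weeks, a constant hazard at 58% one-year admission-free survival in both arms, and no offsetting selection. The range of 0.90 to 0.72 needs a threefold early hazard, for which the article gives no evidence. Judging contacts per week in HT largely removes the shift as long as shortfalls are unrelated to admission. If low-contact patients mainly have a good prognosis, the direction can reverse, so the sign cannot be taken as known. Complete cases is unclear for this endpoint, a separate and smaller defect whose effect cannot be sized from the article.

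The confirmatory ITT result is untouched. The wording should still be changed before analysis, because the PP estimate as described could not safely be read as the effect of peer support when delivered.

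**What to change.** In the analysis plan, before the code is broken:

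1. Judge contact adequacy against the article's weekly minimum, only over HT time up to discharge or first admission, whichever comes first. Contacts missed because HT ended in the event do not count as a shortfall, and contacts made after the event do not count towards adequacy.
2. Name any peer support contact as the control-arm violation. This makes the set's definition explicit for both arms; it does not by itself cure the early-admission problem, which item 1 addresses.
3. Delete complete cases for the primary endpoint, or define it for a censored time.
4. Label the PP hazard ratio as descriptive.

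Optionally, add a complier-average effect on 12-month admission-free survival with randomisation as the instrument. It keeps the randomised comparison, but its confidence interval is wider.

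The cost is a few sentences and a small amount of programming. Contact counts, day of first peer contact and treatment days are already recorded. If contact dates are not held individually, they would be needed to separate contacts before and after the event. Enrolment, sample size and the primary analysis do not change.
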